## Abstract

**Background:**

There is an increasing trend towards shorter hospital stays after transcatheter aortic valve implantation (TAVI), in particular for patients undergoing the procedure via transfemoral (TF) access. Preliminary data suggest that there exists a population of patients that can be discharged safely very early after TF-TAVI. However, current evidence is limited to few retrospective studies, encompassing relatively small sample sizes.

**Methods:**

The Feasibility And Safety of early discharge after Transfemoral TAVI (FAST-TAVI) registry is a prospective observational registry that will be conducted at 10 sites across Italy, the Netherlands and the UK. Patients will be included if they have been scheduled to undergo TF-TAVI with the balloon-expandable SAPIEN 3 transcatheter heart valve (THV; Edwards Lifesciences, Irvine, CA). The primary endpoint is a composite of all-cause mortality, vascular-access-related complications, permanent pacemaker implantation, stroke, re-hospitalisation due to cardiac reasons, kidney failure and major bleeding, occurring during the first 30 days after hospital discharge. Patients will be stratified according to whether they were high or low risk for early discharge (≤3 days) (following pre-specified criteria), and according to whether or not they were discharged early. Secondary endpoints will include time-to-event (Kaplan–Meier) analysis for the primary outcome and its individual components, analysis of the relative costs of early and late discharge, and changes in short- and long-term quality of life. Multivariate logistic regression will be used to identify factors that indicate that a patient may be suitable for early discharge.

**Discussion:**

The data gathered in the FAST-TAVI registry should help to clarify the safety of early discharge after TF-TAVI and to identify patient and procedural characteristics that make early discharge from hospital a safe and cost-effective strategy.

**Trial registration:**

ClinicalTrials.gov Identifier: NCT02404467 (registration first received March 23rd 2015).

## Background

Transcatheter aortic valve implantation (TAVI) is a feasible alternative to surgical aortic valve replacement (SAVR) for patients who are at prohibitively high risk for open surgery. More recently, there has been a trend towards performing TAVI in lower-risk patients, with similar rates of all-cause mortality reported in a randomised trial comparing TAVI with SAVR in intermediate risk patients [1]. The cost-effectiveness of TAVI compared to SAVR has been shown to be acceptable in high-risk patients, especially when transfemoral (TF) access is utilised [2]. However, in a real-world setting, the high cost of TAVI, mainly due to the price of the transcatheter heart valve (THV), limits extension of the procedure to lower risk patients [3].

Hospitalisation is the main contributor to the costs of SAVR, and the second largest contributor to the costs of TAVI [4]. While there is limited scope for reducing the length of hospital stay after open surgery, increasing use of a minimalist approach to TAVI has the potential to significantly reduce the time to discharge. When TF access is used, the procedure can often be performed in a catheterisation laboratory, with use of local anaesthesia and conscious sedation rather than general anaesthesia. This approach reduces the costs of the procedure itself and allows for a shorter stay in the intensive care unit (ICU) and the potential for early discharge from hospital [5–7]. Indeed, there has been a significant decreasing trend in length of hospital stay after TAVI [8, 9], with a recent study reporting an average of 4 days after TF-TAVI at a centre that actively pursued early discharge [10].

A number of studies have evaluated the safety of early discharge after TAVI [8, 11, 12]. Lauck et al. retrospectively evaluated data from 393 TAVI patients, 38% of whom had been discharged within 48 h after their procedure. They found no differences in terms of 30-day mortality, rehospitalisation or disabling stroke between the early and standard discharge groups [11]. Similarly, Durand et al. reported discharge within 72 h for 36% of their 337 TF-TAVI patients, with no difference in 30-day mortality or rehospitalisation [8].

In a small prospective study (*N* = 130), early discharge was specifically targeted after elective TF-TAVI [10]. A total of 59% of patients were successfully discharged within 72 h, with one death and 3 cases of rehospitalisation occurring during the subsequent 30 days. While no death occurred in the patients that were discharged after 72 h, 7 required rehospitalisation. In a cohort of 120 patients that underwent TAVI at a single centre, 21.7% of patients were discharged on either the same day as the procedure or the following day, with a further 32.5% discharged at 2 or 3 days [6]. There were no deaths within 30 days for any of these patients, while mortality was 5.5% for those that were discharged after 4 days. Rehospitalisation rates did not differ significantly between groups.

These studies have provided preliminary data in support of the feasibility and safety of early discharge after TF-TAVI. However, if this approach is to be more widely adopted, there is a clear need for larger, prospective multicentre studies. A substantial cohort of TAVI patients would also allow for evaluation of baseline and procedural characteristics that may indicate suitability for early discharge, further decreasing the associated risks. Furthermore, the rapid advancements being made in THV and implantation technologies make up-to-date information essential.

The Feasibility And Safety of early discharge after Transfemoral-TAVI (FAST-TAVI) registry has been designed in order to provide contemporary data regarding early discharge after TAVI. This prospective, multicentre study will evaluate patients undergoing TF-TAVI with the latest generation of the balloon-expandable SAPIEN THV (SAPIEN 3; Edwards Lifesciences). In addition to assessing adverse outcomes after discharge, the dataset will enable the identification of criteria that will allow safe early discharge of patients after TF TAVI.

## Methods/design

FAST-TAVI is an observational, prospective, multicentre registry that will be performed at 5 sites in Italy (Catania, Bari, Novara, Bologna and Mercogliano), 2 sites in the Netherlands (Amsterdam & Leiden), and 3 sites in the UK (Belfast, Cambridge, Middlesbrough). Approximately 50 patients undergoing TF-TAVI with the SAPIEN 3 THV will be enrolled at each site.

### Patients

Patients undergoing TF-TAVI with the SAPIEN 3 THV (Edwards Lifesciences) will be enrolled on a consecutive basis. The decision to perform this procedure will be made by the Heart Team at each institution according to standard practice; it will not be influenced in any way by the investigators. Beyond the applicable criteria of the device Instructions for Use, no other inclusion or exclusion criteria will be applied.

### Data collection

Data will be collected prospectively according to the timetable set out in Table 1, and will be entered in a standardised case report form (CRF). At baseline, demographic and clinical characteristics will be documented. Laboratory data from blood and urine analysis will be collected and an echocardiogram and an ECG will be performed. Patients will also undergo a full physical examination. A mini-mental state examination (MMSE) will be carried out and patients will be asked to complete the SF-12 QoL (Quality of life) questionnaire (version 2.0). Procedural characteristics, including any complications, will be collected. Post-procedure, patients will be monitored according to standard practice. An echocardiogram and an ECG will be acquired within 2 h of the procedure, and at least once prior to discharge. A physical examination and blood and urine analysis will be performed at daily intervals until discharge.

**Table 1 Tab1:** Data collection timetable

	Baseline	Procedure (up to 2 h post-TAVI)	Day 1	Day 2^c^	Day 3^c^	Discharge	30 ± 12 days	12 months
Informed consent	x							
Demographics	x							
Clinical characteristics	x							
Physical examination^a^	x		x	x	x	x	x	x
Laboratory analysis^b^	x		x	x	x	x		
Current medication	x					x	x	x
ECG	x	x	x	x	x	x	x	x
Echocardiogram	x	x	x			x	x	x
MMSE	x							
SF-12	x						x	x
Clinical event assessment		x				x	x	x

Legend: ECG, electrocardiogram; MMSE, mini-mental state examination; SF-12, short-form-12 quality of life questionnaire. ^a^Includes symptoms, mobility, self-care; ^b^includes blood and urine analysis (complete blood count, electrolytes, renal function etc.); ^c^if still in hospital

Patients will be discharged when it is deemed appropriate by the treating physician. This will be unaffected by their participation in the registry. The length of hospital stay will be documented. Follow-up visits will be conducted in accordance with hospital protocol. Data regarding events during the first 30 ± 12 days after discharge will be collected at next visit after this time point. These will include the components set out in the Valve Academic Research Consortium (VARC)-2 consensus document [13]. An echocardiogram and an ECG will be obtained and a full physical examination will be carried out. Furthermore, patients will be asked to again complete the SF-12 QoL questionnaire.

Further follow-up information will be collected at 12 months post-TAVI. This will include the results of a physical examination, blood and urine analysis, echocardiography and an ECG. Any adverse events or rehospitalisation during the 12 months since TAVI will be recorded.

### Patient stratification

Patients will be stratified when data collection for all patients is complete. A patient will be classified as being at low risk for early discharge if they fulfil all of the criteria at the point of leaving hospital, as displayed in Table 2. The patients will be further stratified according to whether they were discharged early (≤3 days post-TAVI) or late (<3 days). This will give 4 groups for comparison purposes. Further time points (e.g. stratification at hospital admission) as well as cut-offs (1, 2 or 4 days etc.) will be explored once data are available.

**Table 2 Tab2:** Patient stratification

A patient will be classified as being at low risk for early discharge if they fulfil all of the following criteria at the point of leaving hospital:
New York Heart Association (NYHA) class ≤ II
No chest pain attributable to cardiac ischaemia
No untreated major arrhythmias
Complications on day 0 to 1, but free of signs or symptoms on day 3
No fever during the last 24 h (infection-related)
Independent mobilisation and capability of self-care
Preserved diuresis (>40 ml/h during the last 24 h)
No unresolved acute kidney injury type 3 (according to VARC-2 criteria)
No red blood cell transfusion during the last 72 h
Stable haemoglobin in 2 consecutive samples (defined as a decrease of no more than 2 mg/dl)
No stroke or transient ischaemic attack (TIA)
No sign of systemic inflammation or infection (clinic or laboratory)
No haemodynamic instability

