### Primary endpoint

The primary endpoint is a composite of all-cause mortality, vascular-access-related complications, permanent pacemaker implantation, stroke, re-hospitalisation due to cardiac reasons, kidney failure and major bleeding, occurring during the first 30 days after hospital discharge.

Cumulative and time-dependent (Kaplan–Meier) incidence of the primary endpoint will be compared between the 4 groups stratified according to suitability for early discharge (according to protocol) and actual discharge.

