### Statistics

As there are few reliable data on early discharge after TAVI, no formal sample size calculation was performed. Based on rates of TAVI procedures being performed, it was estimated that approximately 50 patients could be recruited in one year at each site.

Intent-to-treat analysis, defined as all patients enrolled in the registry, will be employed. Subjects will be considered registry participants when they enter the catheterisation laboratory/hybrid suite/operating room. Descriptive data summaries will be used to present and summarise the collected data. For categorical variables, frequency distributions will be given. For numeric variables, means and standard deviations or medians and interquartile ranges will be calculated, depending on data distribution. Kaplan–Meier analysis will be performed for time-to-event outcomes. Multivariate logistic regression will be performed to identify predictors of the primary endpoint in the patients discharged early, and predictors of early discharge. Variables entered into the analysis will include baseline characteristics and periprocedural complications.

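### Late discharge is printed as <3 days, which falls inside early discharge (≤3 days) and leaves stays beyond day 3 in neither group

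*Protocol article*

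**What the plan says.** The Patient stratification section crosses two classifications: low or high risk for early discharge, and early or late actual discharge. For the second, patients are "stratified according to whether they were discharged early (≤3 days post-TAVI) or late (<3 days"). The section then concludes: "This will give 4 groups for comparison purposes".

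The abstract (Methods) describes the same stratification but gives only one cut-off. Patients are split by whether they were "high or low risk for early discharge (≤3 days) (following pre-specified criteria), and according to whether or not they were discharged early". It prints no separate limit for late discharge.

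The Primary endpoint section uses the groups directly: cumulative and Kaplan–Meier incidence "will be compared between the 4 groups stratified according to suitability for early discharge (according to protocol) and actual discharge". The Secondary endpoints section uses the same four groups for the individual components, and the abstract lists a comparison of the costs of early and late discharge.

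**The concern.** Two categories meant to divide a cohort must be mutually exclusive and must together cover everyone. As printed, these do neither. The late interval is a subset of the early interval, so an early-versus-late contrast would set a group against part of itself, and the patients with the longest stays would be in no group.

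The sentence is an operative definition in the methods, not background. It is the only place in the article where late discharge has a numerical limit, and the primary comparison depends on it. The same section says that stratification follows complete data collection and that other cut-offs will be explored once data are available. The main cut-off should therefore be beyond doubt beforehand, so that the primary split can be told apart from exploratory ones.

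**Working it through.** **Inputs**

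- Early: ≤3 days post-TAVI (Patient stratification; same threshold in the abstract).
- Late: <3 days (Patient stratification).
- Stated number of groups: 4 (Patient stratification; Primary endpoint).
- Sites: 10, from "prospective observational registry that will be conducted at 10 sites across Italy, the Netherlands and the UK". The list in Methods/design agrees: 5 + 2 + 3 = 10.
- Enrolment: "Approximately 50 patients undergoing TF-TAVI with the SAPIEN 3 THV will be enrolled at each site".
- Early-discharge shares in the cited series (Background): 36% within 72 h in a retrospective transfemoral study of 337 patients; 59% within 72 h in a prospective study of 130; 21.7% on day 0 or 1 plus 32.5% on day 2 or 3 in a single-centre cohort of 120.

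There is no power calculation to reproduce, since "no formal sample size calculation was performed". The figure to test is the stated four groups.

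**Step 1. Classify each discharge day (d)**

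| Discharge day | Early (d ≤ 3) | Late as printed (d < 3) | Groups as printed | Groups if late is d > 3 |
|---|---|---|---|---|
| 0 | yes | yes | 2 | 1 |
| 1 | yes | yes | 2 | 1 |
| 2 | yes | yes | 2 | 1 |
| 3 | yes | no | 1 | 1 |
| 4 and later | no | no | 0 | 1 |

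As printed, only day 3 is classified uniquely. Crossing this with low and high risk does not give four disjoint groups, so the stated 4 is not reproduced. With late as >3 days, every day falls in exactly one discharge group, and 2 risk levels × 2 discharge levels = 4.

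**Step 2. Compare with the rest of the article**

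The abstract splits patients into those discharged early and those not. That makes late the complement of ≤3 days, which is >3 days. The four-group statement works only under that reading.

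**Step 3. Size of the literal reading**

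Planned total: 10 × 50 = 500, approximately. Unclassified = 500 × (1 − share discharged by day 3), treating 72 h as three days:

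- share 59%: 500 × 0.41 = 205
- share 21.7% + 32.5% = 54.2%: 500 × 0.458 = 229
- share 36%: 500 × 0.64 = 320

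The range is about 205 to 320 of 500, or 41% to 64%. These shares come from other centres, and two are 72-h rates while the third is a count of days. That they apply to this registry is an assumption. They do not separate day 3 from days 0 to 2, so they do not size the doubly classified group.

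**Step 4. Which analyses use the late label**

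- Affected: the four-group primary comparison, the four-group component comparisons, and the early-versus-late cost comparison.
- Not affected: the two regressions in the Statistics section. One is restricted to patients discharged early. The other models early discharge, for which the contrast is simply early against not early. Both need only the ≤3-day threshold, which is consistent.

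**The case against.** The strongest reply is that nobody would be misled. The abstract's wording and the four-group statement both point to late as the complement of early. The exploratory cut-offs are given as single days, which also implies one dividing line. An analyst who programmed the printed rule would see at once that four groups did not emerge. Length of stay is recorded for every patient and the grouping is derived after data collection, so nothing is lost and the correct split can be made at any time. Discharge is decided by the treating physician regardless of the registry, so no patient's care depends on the sign. All of this stands. It limits the likely effect on the results, but the printed definition remains wrong.

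A reader might infer several stronger things, which the article does not support:

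- *The definition of the exposure is reversed.* It is not. The early threshold is the same in the abstract and the methods; only the sign on the comparator is wrong.
- *The regressions are compromised.* They use only the early definition.
- *The registry will lose 205 to 320 patients.* That follows only if the printed rule is applied literally and the shares from other centres hold here.
- *The article must also choose between calendar days and 72 h.* That is derivation detail which an article may leave to the full protocol or analysis plan, neither of which is shown.

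An artefact of text extraction is unlikely, since the same sentence prints ≤ correctly and Table 2 in that section prints >40 ml/h correctly. A typesetting slip cannot be excluded, but the published text would need the same correction.

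**Conclusion.** The late-discharge definition is wrong as written. It contradicts the stated four groups in its own section and the complementary split in the abstract. It is very probably a sign error with a recoverable intent, so the practical effect is small if the analysis follows the abstract.

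It deserves correction because it is the only numerical limit for a group used in the primary comparison. The literal-reading figure of 41% to 64% unclassified shows what the printed rule would do under borrowed discharge shares; it does not predict what the analysis will do. The logical finding, that days 0 to 2 fall in both groups and day 4 onward in neither, rests on no assumption beyond the printed signs.

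**What to change.** In Patient stratification, change the late limit from <3 days to >3 days post-TAVI. This matches the abstract and restores four disjoint groups. Then check that the programmed derivation takes late as the complement of ≤3 days.

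The cost is one character plus the words post-TAVI in the text, and one check of the derivation. No data collection, sample size or clinical procedure changes, because this is a classification applied at analysis.

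### Two of the 13 all-must-hold criteria in Table 2 are wrong as printed (the haemoglobin limit, and the complications line with its day-3 check), so the low/high-risk axis of the primary comparison cannot be derived from the text as it stands.

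*Protocol article*

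**What the plan says.** The section on patient stratification joins the criteria by a strict rule: "A patient will be classified as being at low risk for early discharge if they fulfil all of the criteria at the point of leaving", meaning at discharge. Table 2 then lists 13 criteria. Two matter here:

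- Haemoglobin: "Stable haemoglobin in 2 consecutive samples (defined as a decrease of no more than 2 mg/dl").
- Complications: "Complications on day 0 to 1, but free of signs or symptoms on day 3".

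The same section counts as early a patient "discharged early (≤3 days post-TAVI"), so early discharge includes days 1 and 2. It also places the stratification after data collection for all patients is complete. Under Data collection, the footnote to Table 1 limits the day-2 and day-3 assessments to patients to whom "if still in hospital" applies.

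The classification is not a side analysis. Under Primary endpoint, incidence will be "compared between the 4 groups stratified according to suitability for early discharge (according to protocol) and actual discharge".

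**The concern.** Table 2 supplies one of the two axes of the primary comparison. Because the criteria are joined by AND, one mis-stated line moves patients out of the low-risk class whatever their other results.

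Three things look wrong in the two lines. The haemoglobin limit is far smaller than a laboratory can be expected to report. The complications line has neither a negation nor an if-any, unlike the other lines on adverse findings, so under the all-must-hold rule a complication reads as a requirement. And that line fixes its check at day 3, although the rule is applied on leaving hospital and early patients may be gone by then.

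At stake is who belongs to the low-risk group, above all the low-risk patients discharged early, whose safety the registry is meant to describe. If the lines are repaired only when patients are stratified, the repair is chosen with outcomes available, and a reader could not reproduce the groups from the published rule.

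**Working it through.** The article gives no sample size or power figure to reproduce on this point. The check is a unit conversion, a sensitivity range and a comparison of passages.

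**1. Unit of the haemoglobin limit.** 2 mg/dl ÷ 1000 = 0.002 g/dl. With results reported to 0.1 g/dl (assumed), 0.002 ÷ 0.1 = 0.02, so the limit is one fiftieth of the smallest recordable change. As printed, the item passes only if the recorded value is unchanged or higher.

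**2. Share failing the haemoglobin item.** The Data collection section gives the sampling interval: "A physical examination and blood and urine analysis will be performed at daily intervals until discharge". Consecutive samples are therefore about one day apart. The distribution of change is not in the document. Assume change D ~ Normal(mean, SD) in g/dl, rounded to 0.1. Then

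- fail as printed = Φ((-0.05 - mean)/SD)
- fail with the same number in g/dl = Φ((-2.05 - mean)/SD)

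| Mean, SD (assumed) | Fail as printed | Fail if g/dl |
|---|---|---|
| 0, 0.6 | 46.7% | 0.03% |
| -0.3, 0.7 | 64.0% | 0.6% |
| -0.5, 0.8 | 71.3% | 2.6% |

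These are three pairings, not the extremes of every combination: mean -0.5 with SD 0.6 gives 77.3% failing as printed (100% - 22.7%). On a wider grid (mean 0 to -1.0, SD 0.4 to 0.8), about 1% to 55% pass as printed and about 90% to 100% pass in g/dl. The size is uncertain; the direction and the gap between the two units are not.

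**3. Complications line, literal reading.** Every criterion must be fulfilled, and this one describes a patient who had a complication on day 0 or 1. A patient without one does not fulfil it.

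**4. Complications line, evident reading.** Take it as tolerating early complications that have resolved. An uncomplicated patient then passes with no day-3 check. For a patient with a day 0-1 complication, the passages still conflict:

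- classification time: on leaving hospital;
- check time in the line: day 3;
- early discharge: day 3 or sooner;
- day-3 data: only for patients still in hospital.

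Such a patient who leaves on day 1 or 2 has no day-3 status, so the item cannot be judged. The section also plans to explore cut-offs of 1 and 2 days, under which every early discharge comes before day 3.

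**5. Both lines applied literally.** Enrolment is given as "Approximately 50 patients undergoing TF-TAVI with the SAPIEN 3 THV will be enrolled at each site"; with 5 + 2 + 3 = 10 sites this is about 500 patients. Assuming independence, the ceiling on the low-risk share before the other 11 criteria is

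P(complication on day 0-1) × P(haemoglobin passes) × P(in hospital on day 3).

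| Assumed inputs | Ceiling | Of 500 |
|---|---|---|
| 0.10 × 0.10 × 0.5 | 0.5% | 2 to 3 |
| 0.20 × 0.30 × 0.5 | 3% | 15 |
| 0.20 × 0.30 × 1.0 | 6% | 30 |
| 0.40 × 0.50 × 1.0 | 20% | 100 |

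All these rates are assumptions.

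**The case against.** The strongest reply is that nobody would execute these lines literally. The haemoglobin unit looks like a slip, the word but in the complications line signals tolerance of resolved problems, and the primary endpoint section refers to suitability according to a full protocol that is not shown. Table 1 also schedules a physical examination, laboratory work and event assessment at discharge, so the data for a correct derivation may already exist. Much of this stands. It limits the harm but leaves the printed rule wrong: nothing elsewhere in the article corrects either line, and the day-3 conflict survives the charitable reading.

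Three stronger readings are tempting and are not supported.

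- *Either line alone empties the low-risk group.* In the three scenarios above, 29% to 53% of patients still pass the haemoglobin item as printed. The severe loss needs both lines, the complications line being read literally.
- *At least 40% of early discharges cannot be classified.* In the 120-patient series described in the Background, 21.7 ÷ (21.7 + 32.5) = 40% of discharges by day 3 were on the same or the next day. That covers all such discharges at one centre. On the evident reading only those with a day 0-1 complication are affected, and the document does not give that share.
- *Class membership will drift between sites.* Stratification happens once, after data collection, which points to a central derivation. The risk lies in analyst discretion at that stage.

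**Conclusion.** The concern holds in this form. Two of the 13 criteria that define the low/high-risk axis of the primary comparison are wrong as printed.

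Three parts follow from the text and unit arithmetic: the limit equals 0.002 g/dl; the literal complications line is not met by uncomplicated patients; and the day-3 check is impossible at discharge for a patient with an early complication who leaves on day 1 or 2. That any recorded fall would fail needs one further assumption, reporting to 0.1 g/dl.

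The sizes rest on assumed distributions and rates: 47% to 71% failing the haemoglobin item in the three scenarios, against 0.03% to 2.6% in g/dl, and a ceiling of 0.5% to 20% when both lines are taken literally. A reader might infer that almost nobody could be low risk; the upper end of that ceiling, 100 of about 500, shows that this depends on the inputs. The realistic consequence is a grouping rule repaired by judgement after outcomes are known, and a low-risk group that cannot be reproduced from the published text. It should be corrected before stratification.

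**What to change.** Before any patient is stratified, and preferably without access to outcomes:

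1. Reconcile both lines with the full protocol and the CRF, and record the result with a date.
2. Correct the haemoglobin unit. g/dl appears intended; the sponsor must confirm both unit and number. No threshold is proposed here.
3. Restate the complications item as a condition: either no complication on day 0-1, or any such complication resolved. Assess it at the same time point as the other criteria, using the discharge examination and event assessment that Table 1 already schedules. The sponsor confirms the final wording.

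The cost is two lines in Table 2 and the matching derivation code. No new data collection is needed if the CRF holds the daily haemoglobin values and the discharge assessment. These are registry classification rules only: the article states that discharge is decided by the treating physician and is not affected by participation.
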